# Multicenter randomized controlled trial and registry study to assess the safety and efficacy of the NanoKnife® system for the ablation of stage 3 pancreatic adenocarcinoma: overview of study protocols

**DOI:** 10.1186/s12885-021-08474-4

**Published:** 2021-07-07

**Keywords:** Pancreatic ductal adenocarcinoma, Locally advanced pancreatic cancer, Irreversible electroporation, NanoKnife system, Ablation, Modified FOLFIRINOX

## Abstract

**Background:**

Irreversible electroporation (IRE) is a local ablation technique utilizing high voltage, low energy direct current to create nanopores in cell membrane which disrupt homeostasis and leads to cell death. Previous reports have suggested IRE may have a role in treating borderline resectable and unresectable Stage 3 pancreatic tumors.

**Methods:**

Patients with Stage 3 pancreatic ductal adenocarcinoma (PDAC) will be enrolled in either a randomized, controlled, multicenter trial (RCT) or a multicenter registry study. Subjects enrolled in the RCT must have no evidence of disease progression after 3 months of modified FOLFIRINOX (mFOLFIRINOX) treatment prior to being randomization to either a control or IRE arm. Post-induction and post-IRE treatment for the control and IRE arms, respectively, will be left to the discretion of the treating physician. The RCT will enroll 528 subjects with 264 per arm and include up to 15 sites. All subjects will be followed for at least 24 months or until death. The registry study will include two cohorts of patients with Stage 3 PDAC, patients who received institutional standard of care (SOC) alone and those treated with IRE in addition to SOC. Both cohorts will be required to have undergone at least 3 months of SOC without progression prior to enrollment. The registry study will enroll 532 patients with 266 patients in each arm. All patients will be followed for at least 24 months or until death. The primary efficacy endpoint for both studies will be overall survival (OS). Co-primary safety endpoints will be 1) time from randomization or enrollment in the registry to death or new onset of Grade 4 adverse event (AE), and (2 high-grade complications defined as any AE or serious AE (SAE) with a CTCAE v5.0 grade of 3 or higher. Secondary endpoints will include progression-free survival, cancer-related pain, quality of life, and procedure-related pain for the IRE arm only.

**Discussion:**

These studies are intended to provide Level 1 clinical evidence and real-world data demonstrating the clinical utility and safety of the use of IRE in combination with chemotherapy in patients with Stage 3 PDAC.

**Trial registration:**

Clinicaltrials.gov NCT03899636 and NCT03899649. Registered April 2, 2019. Food and Drug Administration (FDA) Investigational Device Exemption (IDE) trial G180278 approved on May 3, 2019.

## Background

The incidence of pancreatic cancer has risen consistently from 1992 to 2020, while the number of deaths due to pancreatic cancer in the United States has also risen proportionately [1]. There will be an estimated 57,600 patients initially diagnosed pancreatic cancer in 2020, representing 3.2% of all new cancer cases. A total of 47,050 deaths due to pancreatic cancer are projected to occur in the U.S. in 2020 representing 7.8% of all cancer deaths [1]. Median overall 5-year survival for patients with Stage 1 and 2 pancreatic cancer has been reported to be 24.4 months while locally advanced pancreatic Stage 3 cancer (LAPC) has a median survival of less 1 year [2, 3]. Patients with Stage 3 pancreatic ductal adenocarcinoma (PDAC) represent 39.2% of the nonmetastatic patient population with an associated 5-year survival of 10.8% [2]. The probability of survival is inversely proportional to tumor size and the number of positive lymph nodes [4].

The current standard of care (SOC) for stage 3 PDAC includes systemic chemotherapy. FOLFIRINOX (combination chemotherapy using 5-fluorouracil [5-FU], leucovorin [folinic acid], irinotecan, and oxaliplatin) has demonstrated improved overall survival to 11.1 months for FOLFIRINOX versus 6.4 months for gemcitabine in metastatic pancreatic cancer, but at the cost of greater toxicity [5]. More recently, a modified form of FOLFIRINOX (without the bolus 5-FU and with a reduced dose of irinotecan) has been shown to have an acceptable safety profile while maintaining comparable efficacy of FOLFIRINOX in metastatic pancreatic cancer [6]. The National Cooperative Cancer Network (NCCN) has recently added modified FOLFIRINOX (mFOLFIRINOX) as a preferred regimen for Stage 3 pancreatic cancer patients with a good performance status (ECOG 0–1) [7].

Although radiation therapy is frequently utilized in the United States for patients with Stage 3 pancreatic cancer, there currently exists a dearth of level 1 evidence demonstrating benefit for radiation or any other local therapy modality. One of the pivotal studies for radiation therapy in this population was the LAP07 prospective randomized trial [8]. In this trial, patients received induction chemotherapy with gemcitabine with or without erlotinib and were then randomized to receive chemoradiation therapy or continue chemotherapy. There was no difference in the primary endpoint of OS although there was decreased local tumor progression in the chemoradiation arm. One major limitation of this trial is that the induction chemotherapy used was not consistent with the current standard of using multiagent combination chemotherapy and it is possible that a more effective systemic induction regimen like mFOLFIRINOX may set the stage for benefit from a local intervention like radiation or ablation.

The poor outcomes among patients with pancreatic cancer has led to the pursuit of new treatment options. Irreversible electroporation or IRE (NanoKnife System, AngioDynamics, Inc., Latham, New York) is a non-thermal based method for local ablation which causes increased permeabilization of the cell membrane through exposure of the cell to electric pulses [9]. Electrodes are placed in a pattern which enables the tumor to be encompassed by the electrical field produced, with electric pulses irreversibly permeating the membranes resulting in cell death. IRE may lead to better preservation of vessels, nerves, and extracellular matrix within or close to the ablated area compared to thermal ablation techniques [10–13].

A growing body of evidence exists on the use of the NanoKnife System to treat pancreatic tumors, including both borderline resectable and unresectable tumors [14–16]. Studies have reported a median OS from diagnosis ranging from 14 to 27 months [17–27] and a median OS from IRE treatment ranging from 10 to 27 months [28–30]. The largest of these studies, a 200-patient, multicenter registry of patients with stage 3 pancreatic cancer treated with IRE via an open surgical approach, reported a median OS of 24.9 months and a median local progression free interval of 10.7 months [21]. Holland et al. recently reported results from a multicenter registry which included 152 patients with LAPC treated with IRE via an open approach at 6 different institutions [31]. Median OS from diagnosis, progression-free survival (PFS), and time to progression (TTP), all from diagnosis were 30.7 months, 22.8 months, and 27.3 months, respectively.

Narayanan et al. reported a retrospective review of 50 patients with LAPC treated with percutaneous IRE (26). Median OS was 27 months (95% confidence interval [CI], 22.7–32.5 months from the time of diagnosis) and 14.2 months (95% CI, 9.7–16.2 months) from the time of IRE. Multivariate analysis demonstrated patients with tumors ≤3 cm had significantly longer median OS than patients with tumors > 3 cm (33.8 vs. 22.7 months from time of diagnosis; *p* = 0.002, and 16.2 vs. 9.9 months from time of IRE; *p* = 0.031). More recently, Ruarus et al. reported the results of the Phase II multicenter PANFIRE II study which prospectively enrolled 50 patients treated with CT-guided percutaneous IRE [25]. This included 40 patients with LAPC and 10 patients with local recurring pancreatic cancer following resection. The median OS from diagnosis for patients with LAPC was 17 months. For patients with local recurrence, the median OS was 16 months from the diagnosis of recurrence and 9 months from IRE treatment. He et al. retrospectively compared 36 patients treated with IRE and 40 patients receiving radiotherapy with both groups receiving 4 months of induction chemotherapy prior to treatment [32]. Following a Propensity Score Matching (PSM) analysis, patients in the IRE group had longer median OS than patients receiving radiotherapy (21.6 months vs. 10.6 months) with significantly greater 1-year (71.4% vs. 41.3%) and 2 year (53.5% vs. 20.7%) OS rates (*p* = 0.011).

Major complications (grade 3 or higher) have been reported in approximately 21 to 34% of patients treated with IRE [16, 25]. This includes the development of portal vein thrombosis, pancreatic fistulae, pancreatitis and hematomas [15].

The above studies have paved the way for conducting two U.S. Food and Drug Administration (FDA) approved Investigational Device Exemption (IDE) studies to prospectively investigate the safety and efficacy of IRE treatment in patients with Stage 3 PDAC, with the goal of establishing level 1 clinical evidence via a RCT and the collection of real-world data via a parallel registry study that facilitates the enrollment of a similar, yet broader, patient population.

## Methods

### Randomized controlled trial (RCT)

The randomized, controlled, 2-arm, unblinded multicenter trial will be conducted at up to 15 sites. After subjects have been treated with 3 months of mFOLFIRINOX and there is no evidence of disease progression, they will be randomized to either a control arm or a treatment arm of IRE with the NanoKnife System using either an open or a percutaneous approach. Randomization will be conducted centrally with subjects randomized in a 1:1 ratio after assessment using a study specified imaging protocol. (Fig. 1). Post-induction treatment in the control arm and post IRE treatment for the IRE arm will be left to the discretion of the treating physician. The mFOLFIRINOX regimen will consist of oxaliplatin at 85 mg/m2, leucovorin at 400 mg/m2, irinotecan at 150 mg/m2 all on day 1, plus 5-FU at 2.4 g/m2 starting on day 1 for 46 h. This regimen will be repeated every 14 days. The minimum period of follow-up for each subject will be for 24 months or until death. Study accrual is estimated to require 36 months to complete with each subject followed until 24 months after enrollment of the last subject, or death.

**Fig. 1 Fig1:**
[figure not shown]
Study Design: Randomized Controlled

### Registry study

The multicenter, observational registry study will include patients with Stage 3 PDAC who received SOC alone and those treated with IRE in addition to SOC (Fig. 2). Both cohorts will be required to undergo at least 3 months of SOC without progression prior to enrollment in the registry. The accrual time for the registry study is 24 months, and each patient will be followed-up for at least 3 months after the study enrolls 266 patients in each cohort. The Registry study will enroll both control and IRE patients from sites where patients are routinely treated with ablation using the NanoKnife System. Additional control patients will also be enrolled from sites that do not offer treatment with the NanoKnife System. The non-NanoKnife sites will be selected to be comparable to the NanoKnife sites with respect to type of center, geography, size, volume of patients with pancreatic cancer, volume of pancreatic cancer surgeries, type of chemotherapy, and duration of chemotherapy.

**Fig. 2 Fig2:**
[figure not shown]
Study design: Registry

#### Study objectives

The primary objectives for both the RCT and registry study are to test the hypothesis that IRE with the NanoKnife System improves OS in subjects with Stage 3 PDAC and to assess the safety of IRE compared to the control arm for the RCT or SOC cohort for the registry study. Secondary objectives include comparing PFS, cancer-related pain and quality of life (QOL) for subjects in the control arm versus the IRE arm and to assess procedure-related pain in subjects in the IRE arm.

#### Key eligibility criteria

The RCT will be limited to subjects with cytologically or pathologically confirmed pancreatic adenocarcinoma that are unresectable and who meet the study’s inclusion/exclusion criteria (Table 1). As compared to the stringent eligibility requirements of the RCT, the registry study will have broader inclusion/exclusion criteria allowing for evaluation of real-world evidence regarding the safety and effectiveness of NanoKnife IRE. Patients who have received a wide variety of prior treatments (chemotherapy, chemoradiation or other procedures) as well as those who choose to receive the IRE treatment rather than get randomized are eligible to participate in the registry study. Subjects must have no evidence of disease progression after completion of the 3 months of induction therapy in order to participate in the RCT and registry. Response Evaluation Criteria In Solid Tumours 1.1 (RECIST 1.1) and pancreatic cancer specific secondary endpoints may be used to assess radiologic and clinical outcomes associated with disease progression. Blinded reads of imaging will be performed in a central location by external blinded readers for both the randomized controlled trial and the registry study.

**Table 1 Tab1:** Patient Inclusion and Exclusion Criteria

Key Inclusion Criteria	
*Randomized Controlled Multicenter Study* ● Signed and dated informed consent form. ● 18 years of age and older. ● Diagnosis of unresectable Stage 3 pancreatic adenocarcinoma cancer cytologically or pathologically confirmed per American Joint Committee on Cancer (AJCC) staging criteria. ● Tumor evaluated as Stage 3 according to National Comprehensive Cancer Network (NCCN) guidelines, based on radiographic imaging or exploratory surgery. ● Maximum axial and anterior to posterior tumor dimension of ≤3.5 cm, after receiving three months of treatment with the mFOLFIRINOX regimen. ● Has received 3 months of treatment with the mFOLFIRINOX regimen. ● Has an Eastern Cooperative Oncology Group (ECOG) performance status of 0 or 1. ● Has an American Society of Anesthesiologists (ASA) classification of physical health status of 1, 2, 3 or 4.	*Multicenter Registry* ● Signed and dated informed consent form ● 18 years of age and older ● Diagnosis of Stage 3 PC cytologically or pathologically confirmed per American Joint Committee on Cancer (AJCC) staging criteria. ● Tumor evaluated as Stage 3 according to National Comprehensive Cancer Network (NCCN) guidelines, based on radiographic imaging or exploratory surgery ● Maximum axial and anterior to posterior tumor dimension of ≤3.5 cm after standard of care. ● Has received 3 months of standard of care per each participating institution’s guidelines ● Has an Eastern Cooperative Oncology Group (ECOG) performance status of 0 or 1. ● Has an American Society of Anesthesiologists (ASA) classification of physical health status of 1, 2, 3 or 4. ● Are at an IRE site and are deemed eligible for IRE and receive ablation using the NanoKnife System. ● Shows no evidence of disease progression based on NCCN guidelines after completing 3 months of standard of care.
Key Exclusion Criteria	
*Randomized Controlled Multicenter Study* ● Subjects who are or may be pregnant as determined by a positive pregnancy test or breastfeeding or male or female patients of reproductive potential who are not willing to employ highly effective birth control from screening to 6 months after the last dose of chemotherapy. ● Unable to tolerate general anesthetic with full skeletal muscle blockade. ● Is actively bleeding, anticoagulated, coagulopathy, or has any of the following hematology results: hemoglobin less than10 g/dL without the support of growth factors or transfusions; absolute neutrophil count less than 1500 cells/mL; or platelet count less than 100,000. ● Has an implanted cardiac pacemaker, defibrillator, electronic device(s) or implanted device(s) with metal parts in the thoracic cavity at the time of IRE. ● Has a history of epilepsy or other neurological diseases. ● Has renal, cardiac, liver, or hematological abnormalities of concern to the investigator. ● Has Stage 3, 4, or 5 chronic kidney disease. ● Is receiving IRE for margin accentuation. ● Has evidence of disease progression at 3 months after FOLFIRINOX treatment. ● Participating in an interventional trial for pancreatic cancer during the study data collection period. ● Did not meet study defined criteria for adequacy of induction treatment at the end of the 3 months.	*Multicenter Registry* ● Participating in an interventional trial for pancreatic cancer during the study data collection period. ● Pregnant or lactating patients or male or female patients of reproductive potential who are not willing to employ highly effective birth control from screening to 6 months after the last dose of chemotherapy ● Unable to tolerate general anesthetic with full skeletal muscle blockade. ● Has an implanted cardiac pacemaker, defibrillator, electronic device(s) or implanted device(s) with metal parts in the thoracic cavity at the time of IRE.

#### Study endpoints and assessments

The primary efficacy endpoint for both the RCT and the registry study will be OS defined as the time (in months) from randomization or enrollment in the registry to the date of death for any reason. Co-primary safety endpoints include time (in months) from randomization or enrollment in the registry to death or new onset of Grade 4 AE, and the development of high-grade complications defined as any AE or SAE with a CTCAE v5.0 grade of 3 or higher.

Secondary endpoints for both studies include a) PFS defined as the time (in months) from randomization or enrollment in the registry to the date of first observed disease progression (per clinical and radiologic criteria), or death from any cause, if death occurs without documented disease progression, b) procedure-related pain in subjects in the IRE arm, as measured by the Brief Pain Inventory (BPI-SHORT FORM) on the day of the procedure and post-procedure days 1, 7, 14 and 30, c) cancer-related pain assessed in the control and IRE arms using the BPI-SHORT FORM at baseline, 3 months, 6 months and at 6-month intervals thereafter, and d) QOL assessed in the control and IRE arms using the EQ-5D questionnaire at baseline, 3 months, 6 months and then at 6-month intervals for the duration of the study.

The registry study will also assess several exploratory endpoints including chemotherapy-free days (after 3 months of SOC), the need for opioids for cancer-related pain, OS from date of pancreatic cancer diagnosis, PFS from date of enrollment, and identification of risk factors and biomarkers associated with outcomes. Additional QOL exploratory endpoints which will be collected include rates of avoidable events associate with chemotherapy in the IRE arm during chemotherapy free days compared to the control arm, unplanned readmissions within 30 days following discharge, and in-hospital mortality.

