Subjects who do not have disease progression and have not died, will be censored at the date of last tumor assessment. Subjects with a single missing radiologic or clinical assessment immediately prior to a visit with documented disease progression (or death) will be analyzed as a PFS event at the time of the clinical or radiologic assessment that shows progression. Subjects with two or more consecutive missing radiologic or clinical assessments immediately prior to an assessment without documented progression (or death) will be censored at the date of last assessment when the subject was documented as progression-free prior to the first of the two or more missing assessments. PFS will be analyzed using similar statistical methods as that for the OS endpoint.

Pain Severity Scores and average Pain Interference Score will be derived for each subject from BPI-SHORT FORM questionnaire. QOL measures will be derived for each subject from the EQ-5D questionnaire, including the EQ Visual Analogue Scale (VAS) and EQ-5D summary index. Both absolute change and percent change from baseline will be analyzed by treatment arm and by study visit for all of the above.

For the primary safety endpoints, a log-rank test will be used to compare the time (in months) from randomization to death or new onset of Grade 4 AEs for the two treatment arms, with data censored at the time of loss to follow up or study discontinuation. The number and proportion of subjects with a high-grade complication defined as any AEs or SAEs with a CTCAEv5.0 grade of 3 or higher will be summarized by treatment arm and CTCAE grade.

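### The article leaves open whether clinical progression alone is a PFS event in an unblinded trial; if it is, the planned blinded imaging reads cannot correct that part of the endpoint

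*Protocol article*

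**What the plan says.** All references are to the protocol article.

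- **Blinding** (Methods, Randomized controlled trial): "The randomized, controlled, 2-arm, unblinded multicenter trial will be conducted at up to 15 sites".
- **Definition of PFS, both studies** (Study endpoints and assessments): time to the "date of first observed disease progression (per clinical and radiologic criteria), or death from any cause".
- **Analysis rule, RCT** (Statistical analysis, Randomized controlled trial): after a single missed assessment, a patient with documented progression "will be analyzed as a PFS event at the time of the clinical or radiologic assessment that shows progression". The rule for two or more missed assessments also joins the two kinds of assessment with *or*.
- **Censoring** (same section): "Subjects who do not have disease progression and have not died, will be censored at the date of last tumor assessment".
- **Criteria** (Key eligibility criteria): RECIST 1.1 and "pancreatic cancer specific secondary endpoints may be used to assess radiologic and clinical outcomes associated with disease progression".
- **Central reading** (same section): "Blinded reads of imaging will be performed in a central location by external blinded readers for both the randomized controlled trial and the registry study". No section links these reads to the PFS event or its date.
- **Status of PFS**: in the RCT it is tested by a two-sided log-rank test at 0.05, only if OS is significant, with assumed medians of 6 and 8 months. The registry also tests PFS only after OS.

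**The concern.** Consider a patient who deteriorates clinically while imaging shows no progression. If both kinds of criteria must be met, that patient has no PFS event yet. If either is enough, the patient has an event on the day of the clinical assessment. The article can be read both ways.

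The choice matters because treatment is known. Clinical progression calls for judgement, and in an unblinded trial that judgement is probably made by someone who knows the arm. Because PFS runs to the first observed progression, an early clinical call fixes the date, and a later blinded scan read does not move it.

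The bias has no fixed sign. An assessor who expects IRE to work may call progression sooner in controls. Conversely, the Background lists pancreatitis, fistulae and hematomas after IRE, and symptoms of these might be taken for progression. That last link is a reviewer's inference, not a statement in the article.

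PFS is the endpoint named after OS in the fixed testing sequence, and the planned gain is only 2 months. Modest arm-dependent shifts in dating are therefore not small against the effect sought.

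**Working it through.** **1. The plan's own figures.** With HR 0.75, two-sided alpha 0.05 and 80% power, Schoenfeld's formula gives 4(1.960 + 0.842)² / (ln 0.75)² = 380 events, as stated for OS.

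For PFS, take 222 patients per arm, uniform accrual over A = 36 months, further follow-up F = 24 months and exponential times with λ = ln 2 / median. The event probability is 1 − [exp(−λF) − exp(−λ(A+F))] / (λA).

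- Median 6 months: 0.985. Median 8 months: 0.962.
- Expected events: 222 × (0.985 + 0.962) ≈ 432.
- Power: Φ(√(432/4) × |ln 0.75| − 1.96) = Φ(2.99 − 1.96) ≈ 0.85.

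This agrees with the stated power of at least 80%. No stated number is wrong; the point concerns the definition.

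**2. The two wordings side by side.**

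| Patient | Both criteria required | Either criterion enough |
|---|---|---|
| Radiologic and clinical progression | Event | Event, dated at whichever comes first |
| Clinical progression only | No event | Event at the clinical assessment |
| Death without progression | Event | Event |

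The second row is where the readings part, and it is the row a blinded image read cannot reach.

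**3. Size of a possible bias, PFS taken alone.** The article gives no share of clinical-only events and no interval by which calls might be early, so both are assumed. Simulation: no true PFS effect, median 6 months in both arms, 222 per arm, no censoring, a share of control events moved earlier, unstratified log-rank test, superiority declared at z < −1.96.

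| Control events called early | By | Apparent HR | False superiority |
|---|---|---|---|
| None | – | 1.00 | 2.5% (nominal) |
| 20% | 1 month | – | 4.5% |
| 20% | 2 months | – | 6.7% |
| 30% | 2 months | 0.94 | 9.8% |
| 50% | 2 months | 0.90 | 19.3% |

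Adding administrative censoring from the 36 + 24 month schedule changes little: 9.5% and 19.4% for the last two rows. The closed form agrees: at HR 0.90, Φ(√108 × 0.1054 − 1.96) = Φ(−0.865) ≈ 19%.

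**4. The opposite direction.** Suppose the true HR is 0.75 and the same distortion falls on the IRE arm. Treating it as a factor on the HR gives 0.75/0.94 ≈ 0.80 or 0.75/0.90 ≈ 0.83. Power falls from 85% to Φ(√108 × 0.223 − 1.96) ≈ 64%, or Φ(√108 × 0.182 − 1.96) ≈ 47%. Direct simulation with 30% or 50% of IRE events called 2 months early gives 67% and 48%.

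**5. The OS gate.** A formal PFS claim needs a significant OS result first. If OS truly does not differ, the chance of a false PFS superiority claim cannot exceed the chance of a false OS win for IRE, about 2.5%. Adding the gate to the simulation in step 3, with assumed post-progression survival equal in both arms (exponential, mean 7 months), turned the last two rows into 1.7% and 2.0%.

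**The case against.** The strongest reply is that there is no conflict. Naming clinical and radiologic criteria together, next to the idea of first observation, can simply mean that both kinds are in use and whichever shows progression first counts. The *or* stands in rules for missed assessments, not in the definition. This is a fair reading, so a reader who infers that the two sections flatly contradict each other goes too far. But on this reading clinical progression alone is an event, which is the case that opens the route to bias.

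A second reply is that nobody is named as the clinical assessor, and that adjudication commonly sits in the full protocol or an imaging charter, which are not shown. This stands: that unblinded site staff make the call is an inference, and the missing name is not itself a finding. What the article does state is an unblinded design, an *or* rule for counting and dating events, and blinded reads limited to images.

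Third, a reader might infer that the central read gives PFS no protection. The article does not support that. If the read governs radiologic progression, it can protect those events under either wording, and death needs no judgement.

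Fourth, the 10% and 19% figures might be taken as the trial's false-positive rate for PFS. They are not: they ignore the OS gate, rest on assumed shares and show one direction only.

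Finally, a purely radiologic PFS has its own weakness. Patients who progress clinically and stop scanning may be censored, and that censoring may be informative. This stands and shapes the fix.

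**Conclusion.** The point holds in a limited form. The article does not settle whether clinical progression alone is a PFS event. If it is, part of a formally tested endpoint can rest on an assessment made with knowledge of the arm, and the planned blinded image reads cannot correct that part.

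The primary endpoint is untouched and the design figures reproduce. If OS truly does not differ, the gate keeps formal false PFS claims near 2.5% or below. The exposure is a biased PFS estimate in either direction, or a false PFS claim after an OS win. In that last case, with a true OS effect but no true PFS effect, the ungated figures (about 4.5% to 19% for the assumed shares and shifts) are a rough guide only.

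The change is worth making before the data are analysed, because it is cheap and the blinded reads are already planned. It is not a flaw that undermines the trial.

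**What to change.** 1. Use one definition of progression in the endpoint section and in the PFS analysis rules.
2. For the formally tested PFS in the RCT, define the event as radiologic progression on the blinded central read, dated at that scan, or death from any cause.
3. Prespecify, as a sensitivity analysis, PFS that also counts clinical-only progression.
4. Do not censor at a clinical progression call. Keep following these patients for PFS to the next scan or death. At least in a sensitivity analysis, count a death after missed scans as an event.
5. Apply the same definition in the registry where scans are available.

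The cost is wording in two sections, since the central reads are already planned. There will be slightly fewer or later events, because a purely clinical progression counts only at a confirming scan or at death. Some risk of informative censoring remains in patients who stop scanning; item 4 reduces it but does not remove it. The two PFS analyses should be reported together so that a reader can see whether the result depends on clinical calls.
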